#### Exclusion Criteria

2.6.2

Patients will be excluded if they have been on ART for less than 6 months, are unable to communicate effectively, have severe hearing impairment, are critically ill, have advanced immunosuppression (CD4 count < 200 cells/mm^3^), or have active tuberculosis, hepatitis C virus (HCV) infection, or active syphilis requiring intensive medical management, as these conditions may confound the study outcomes.

### Sample Size Determination

2.7

The sample size for this pilot quasi‐experimental study was determined based on the primary outcome, treated as a continuous variable (such as reduction in HIV viral load, adherence score, or knowledge score). Since measurements will be taken at baseline and endline in both intervention and comparison groups, the intervention effect will be evaluated by comparing mean changes in outcome between groups using a paired *t*‐test and a difference‐in‐differences approach [18].

The required sample size was calculated using the standard formula for comparing mean differences between two independent groups [19, 20].

The sample size for this study was determined using the formula for comparing two means: n = 2σ^2^(Z_a/2_ + Z_β_)^2^/Δ^2^

where (n) represents the required sample size per group, Z_a/2_ is the critical value corresponding to the desired significance level, (Z_β_) is the critical value corresponding to the desired statistical power, σ is the standard deviation of the change score, (σ^2^) is the variance of the change score, and Δ is the expected mean difference between the intervention and comparison groups. For this study, a significance level of 5% (α = 0.05) was assumed, corresponding to a critical value of (Z_a/2_ = 1.96), while a statistical power of 80% was used, corresponding to (Z_β_ = 0.84). The standard deviation of the change score was assumed to be 15, and the expected mean difference between the two groups was 8.4. Substituting these values into the formula gave; n = 2(15)^2^(1.96 + 0.84)^2^/8.4^2^

The variance was first calculated as (15^2^ = 225), and the sum of the Z‐values was (1.96 + 0.84 = 2.80), which when squared gave 7.84. Multiplying the numerator resulted in (2 × 225 × 7.84 = 3528), while the denominator was calculated as (8.4^2^ = 70.56). Dividing the numerator by the denominator gave (n = 3528/70.56 = 49.99), which was rounded up to 50 participants per group. To account for an anticipated 20% loss to follow‐up, the sample size was adjusted using the formula (n _adjusted_ = n/1–r), where (r) represents the expected attrition rate. Substituting the values yielded (n _adjusted_ = 50/0.80 = 62.5). For operational feasibility and balanced allocation, this was rounded to 60 participants per group. Therefore, the final sample size for the study was 120 participants, with 60 participants in each group.

Thus, a total of 120 HIV–HBV co‐infected participants will be enrolled, with 60 participants in the intervention group and 60 participants in the comparison group. This sample size is also adequate for evaluating feasibility outcomes, including recruitment, retention, intervention acceptability, and preliminary effectiveness in this pilot study [21, 22].

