#### Primary Objective

2.1.1

The primary objective of this study is to evaluate the effect of a patient‐centered education program on HIV virological outcomes among adults living with HIV‐HBV co‐infection. The corresponding primary outcome will be the change in plasma HIV RNA viral load, measured as log‐transformed HIV viral load (log_10_ copies/mL) from baseline to the end of the 6‐month follow‐up period. This outcome will be assessed using plasma HIV RNA viral load testing to quantify changes in virological response over time. In addition, HIV virological suppression, defined as a plasma HIV viral load of < 1000 copies/mL, will be evaluated as a secondary clinical outcome at the end of follow‐up.

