#### The Health Belief Model Questionnaires

2.12.3

Data on participants' knowledge regarding HIV–HBV co‐infection and Health Belief Model (HBM) constructs will be collected at baseline (enrollment) and at the end of the 6‐month follow‐up period using a structured interviewer‐administered questionnaire. The questionnaire will assess knowledge (15 items) and the six core HBM domains, including perceived susceptibility (8 items), perceived severity (7 items), perceived benefits (8 items), perceived barriers (7 items), self‐efficacy (8 items), and cues to action (6 items).

Responses to HBM items will be measured using a 5‐point Likert scale ranging from 1 (strongly disagree) to 5 (strongly agree), reflecting participants' perceptions, beliefs, motivation, and confidence regarding adherence to recommended HIV–HBV‐related health behaviors, including medication adherence, clinic attendance, and self‐management practices. Knowledge items will be scored based on correct responses, and a composite knowledge score will be generated, with higher scores indicating better knowledge. Composite scores will also be calculated for each HBM construct by summing item responses, with higher scores indicating stronger beliefs within the respective domains. Changes in knowledge and HBM construct scores between baseline and the 6‐month follow‐up assessment will be evaluated to determine the effect of the patient‐centered education intervention [27].

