## Limitations of the Study

4

As this is a pilot quasi‐experimental study with a relatively small sample size, the study may have limited statistical power to detect statistically significant differences in HIV virological outcomes between the intervention and comparison groups. Therefore, the findings should be interpreted cautiously, as the study is primarily intended to evaluate feasibility, acceptability, and generate preliminary estimates of intervention effects to inform the design and sample size calculation of future adequately powered studies. In addition, baseline HIV drug resistance testing, systematic TB screening, and longitudinal ALT monitoring were not performed because of resource and laboratory constraints. Consequently, adherence‐related virological failure could not be distinguished from resistance‐related failure, and liver safety outcomes could not be evaluated. Furthermore, validated measures of HIV‐related stigma and depression were not included, which may have limited the assessment of important behavioral and psychosocial factors influencing medication adherence and virological outcomes. These factors should be considered in future studies.

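### The 80% power in section 2.7 is not shown for the primary outcome: an SD of 15 and a difference of 8.4 cannot be changes in log10 HIV RNA

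*Protocol article*

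**What the plan says.** Section 2.7 (Sample Size Determination) bases the size on the primary outcome, which it describes as "treated as a continuous variable (such as reduction in HIV viral load, adherence score, or knowledge score". It applies the two-means formula with a two-sided 5% level and 80% power. The inputs are: "The standard deviation of the change score was assumed to be 15, and the expected mean difference between the two groups was 8.4". No unit is attached to either number, and the references cited there support the approach and the formula, not these values.

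Elsewhere the primary outcome is not open. Section 2.1.1 (Primary Objective) gives it as change in plasma HIV RNA, "measured as log‐transformed HIV viral load (log_10_ copies/mL) from baseline to the end of the 6‐month follow‐up period". The abstract and sections 2.5, 2.10.1 and 2.12.4 agree. Medication adherence and knowledge are secondary outcomes (section 2.1.2).

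The formula gives 50 per group. Section 2.7 then allows for 20% loss by dividing by 0.80, obtains 62.5, and continues: "For operational feasibility and balanced allocation, this was rounded to 60 participants per group". The total is 120.

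Section 4 (Limitations) adds that "the study may have limited statistical power to detect statistically significant differences in HIV virological outcomes".

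**The concern.** A power statement holds for an outcome only if the SD and the target difference are on that outcome's scale. Here the text names the primary outcome, offers three different scales as examples of it, and uses numbers that cannot belong to the one the trial has chosen.

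The article sets formal hypotheses about viral load (sections 2.3 and 2.4) and declares significance at p < 0.05 (section 2.15). A reader will want to know what difference in log10 viral load the trial could detect, and section 2.7 does not say. The investigators also cannot check during the study whether the observed variability matches the design, since no variability on the analysis scale was assumed.

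**Working it through.** **Inputs from section 2.7.** Two-sided α = 0.05 (z = 1.96); power 80% (z = 0.84); SD of change 15; difference 8.4; loss 20%; 1:1 allocation. From section 2.6.1: baseline viral load at least 1000 copies/mL, that is, at least 3 log10.

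**1. The plan's own figure reproduces.** n = 2 × SD² × (1.96 + 0.84)² / Δ² = 2 × 225 × 7.84 / 70.56 = 3528 / 70.56 = 50.0 per group. The fault is in the inputs, not in this arithmetic.

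**2. Can 8.4 and 15 be log10 copies/mL?**
- Difference: 10^8.4 ≈ 2.5 × 10⁸, about a 250-million-fold ratio between the groups' changes.
- SD: the SD of any variable is at most about half its range, so an SD of 15 needs changes spanning about 30 log10. As an illustration, assume an extreme measurable range of 1.3 to 7 log10 (the article gives none). With baseline at least 3, change lies between 1.3 − 7 = −5.7 and 7 − 3 = +4.0. The range is 9.7, so the SD cannot exceed about 9.7/2 ≈ 4.9.

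Neither figure is possible on the primary-outcome scale.

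**3. Do other readings rescue them?** On raw copies/mL, a target difference of 8.4 copies is not a meaningful effect when every baseline is at least 1000. For the knowledge score, section 2.12.3 says "The questionnaire will assess knowledge (15 items"; at one point per item, change runs from −15 to +15, and an SD of 15 is the mathematical maximum, reached only if half the patients go from 0 to 15 and half from 15 to 0. The adherence scale might fit, but adherence is a secondary outcome.

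**4. What the formula actually uses.** Only the ratio matters: 8.4/15 = 0.56 SD. The same n would serve log10 viral load if 0.56 SD were a justified target there. The article does not argue this.

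**5. Attrition.** 50/0.80 = 62.5, so 63 per group. With 60 per group, 60 × 0.80 = 48 remain. Power at 0.56 SD with 48 per group: 0.56 × √(48/2) = 2.743; Φ(2.743 − 1.96) = 78.3% (normal approximation), or 77.5% (t-test). At 50 per group the figures are 80.0% and 79.2%. Keeping 50 of 60 requires loss of at most 1 − 50/60 = 16.7%.

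**6. What 48 evaluable per group can detect with 80% power.** Normal approximation: 2.8 × √(2/48) = 0.572 SD. t-test: 0.578 SD. The SD of log10 change is not in the article, so the values below are assumptions.

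| Assumed SD (log10) | Detectable difference, 0.578 × SD (log10) | Power if the true difference were 0.5 log10 (also assumed; normal approximation) |
|---|---|---|
| 0.5 | 0.29 | 99.8% |
| 0.8 | 0.46 | 86.5% |
| 1.0 | 0.58 | 68.8% |
| 1.2 | 0.69 | 53.2% |
| 1.5 | 0.87 | 37.2% |

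The last column runs from almost certain detection to little better than one in three, so without an SD the power for the primary outcome cannot be stated.

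**The case against.** **Only the ratio matters.** True: 0.56 SD is an ordinary standardised effect, and 60 per group may turn out sufficient. This is why the point must be that power is not shown, rather than that it is low. A reader might infer that the trial could detect only a large viral-load difference. The article does not support that, since it gives no SD of log10 change, and at an assumed SD of 0.5 the detectable difference is 0.29 log10. Equally, section 2.7 does not present a standardised effect; it states an SD and a mean difference for the primary outcome.

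**The study is a pilot and says so.** Section 2.15 puts the weight on magnitude and precision rather than significance alone, and section 4 asks for cautious interpretation. This stands, and it reduces the risk that a null result is over-read. It does not make the printed calculation correct.

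**Section 4 might be read as contradicting section 2.7.** It does not. A caution that power may be limited can stand beside a design target of 80% under stated assumptions.

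**The rounding is disclosed.** Section 2.7 prints 62.5, then 60, and gives a reason. The loss is under 2 percentage points by the normal approximation, so this is secondary. What remains is that 60 per group does not cover the 20% loss that the same paragraph allows for.

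**Conclusion.** Wrong as written. Section 2.7 states 80% power for the primary outcome from an SD and a difference that are impossible in log10 copies/mL. That conclusion needs no outside figure; the 1.3 to 7 log10 range only illustrates how far off the SD is. True power for the primary outcome is unknown and may be above or below 80%. The minor point is exact: 62.5 (63) per group is needed on the plan's own rule, 60 is used, and 48 remain against 50, giving 78.3% (normal) or 77.5% (t) at 0.56 SD. Those percentages belong to the standardised effect and say nothing about viral load unless 0.56 SD is justified there.

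**What to change.** In section 2.7:

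- Base the calculation on change in log10 HIV RNA alone, and delete the list that offers adherence or knowledge score as alternatives.
- State the SD of log10 change with its source, or as an assumption with a range.
- Keep 60 per group, and replace the 80% power claim with the difference detectable at 48 evaluable per group: about 0.58 × SD, shown across the assumed range as in the table above.
- If the 0.56 SD calculation is kept, say that it is a standardised effect not derived from viral load, and that it gives about 78% power with 20% loss.

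The cost is rewording one section. No extra patients are needed. The abstract states no power, so it does not change, and section 4 can stay as it is.

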### Sampling Method and Subject Recruitment

2.8

Because this is a pilot quasi‐experimental study, participants will not be randomly allocated to intervention and comparison groups. Instead, the selected hospitals will be purposively assigned to either the intervention or comparison group based on service capacity, logistical feasibility, and the need to minimize contamination between study arms. The University of Gondar Comprehensive Specialized Hospital will serve as the intervention site, where participants will receive the patient‐centered education intervention integrated into routine ART services, while Felege Hiwot Comprehensive Specialized Hospital will serve as the comparison site, where participants will continue receiving standard HIV care.

Within each study site, eligible participants will be selected using simple random sampling. After obtaining the necessary institutional permissions, a sampling frame consisting of all eligible adults living with HIV–HBV co‐infection receiving ART will be obtained from the respective hospitals. Each eligible participant will be assigned a unique identification number, and participants will be selected using a computer‐generated random number method until the required sample size for each study arm is reached.

Blinding of participants and intervention providers will not be feasible because of the nature of the educational intervention. Therefore, this study will be conducted as an open‐label trial. To minimize potential bias, standardized intervention delivery procedures, uniform data collection protocols, and structured outcome assessment tools will be used across both study sites. In addition, primary outcome assessments will rely primarily on objective clinical measures, including laboratory‐confirmed HIV viral load results and routinely documented medical records, whenever possible. Although the principal investigator and data analyst will be aware of group allocation, outcome assessment and data verification procedures will be standardized to reduce measurement and analytical bias.

### Description of Intervention Package

2.9

#### Patient‐Centered Health Education Intervention

2.9.1

The intervention selected for this study is a patient‐centered health education intervention designed to improve HIV‐related clinical outcomes among adults living with HIV receiving ART. The intervention package consists of structured patient‐centered health education, medication adherence counseling, behavioral counseling, and self‐management support integrated into routine ART services. The primary goals of the intervention are to improve HIV virological outcomes, enhance medication adherence, strengthen self‐management practices, increase disease‐related knowledge, promote healthy behavioral changes, and improve retention in care.

Following participant enrollment, six healthcare professionals from the selected hospitals, including nurses, pharmacists, and clinicians involved in HIV care, will undergo a 3‐day training program. The training will focus on patient‐centered communication, HIV management, medication adherence counseling, behavioral change strategies, and delivery of standardized health education materials to ensure consistent intervention implementation.

Participants in the intervention group will receive structured education sessions over a 6‐month period during routine ART clinic visits. The initial session will last approximately 40–60 min and will cover general information about HIV‐HBV co‐infection, treatment goals, medication adherence, viral load monitoring, risk reduction strategies, and self‐management practices. Subsequent follow‐up sessions will be conducted monthly, with each session lasting approximately 20–30 min, to reinforce key messages, address barriers to adherence, provide individualized counseling, and support behavioral change.

Educational sessions will be delivered using standardized counseling guides, visual educational materials, and interactive discussions tailored to participants' needs, literacy levels, and clinical circumstances. Family members or treatment supporters may be involved in selected sessions, where appropriate, to strengthen adherence support. A detailed description of the intervention components, delivery procedures, and educational content will be provided following completion of the pilot study.

#### Behavioral Counseling Intervention

2.9.2

Healthcare professionals (HCPs) will deliver the patient‐centered education intervention using the Health Belief Model (HBM) as the guiding behavioral framework. The intervention will address the core HBM constructs, including perceived susceptibility, perceived severity, perceived benefits, perceived barriers, self‐efficacy, and cues to action, to promote positive health behaviors among adults living with HIV‐HBV co‐infection.

Educational sessions will focus on improving participants' knowledge and understanding of HIV‐HBV co‐infection, including disease transmission, prevention, treatment, and long‐term management. Participants will receive information on the modes of transmission of HIV and HBV, including transmission through unprotected sexual contact, blood exposure, needle sharing, and mother‐to‐child transmission, as well as clarification of common misconceptions regarding non‐transmission through casual contact such as hugging, handshaking, sharing food utensils, or being near someone who coughs or sneezes.

The intervention will also address the chronic nature of HIV and HBV infection, the potential for disease progression and complications in the absence of treatment, and the increased risk of opportunistic infections, liver disease, cirrhosis, and hepatocellular carcinoma among individuals with HIV‐HBV co‐infection. Healthcare professionals will emphasize the benefits of early diagnosis, lifelong adherence to ART and HBV‐active medications, regular clinical follow‐up, and routine laboratory monitoring, including viral load assessment and liver function evaluation.

In addition, the educational intervention will address stigma, psychosocial barriers, and misconceptions that may negatively affect treatment adherence and healthcare‐seeking behavior. Counseling sessions will aim to strengthen patients' confidence in managing their condition, improve medication adherence, encourage retention in care, and promote self‐management practices through personalized goal setting, problem‐solving strategies, and ongoing motivational support.

#### Medication Adherence Counseling

2.9.3

Participants will receive structured education and counseling from trained healthcare professionals on the importance of taking medications as prescribed, the potential consequences of poor medication adherence, and the clinical benefits of maintaining optimal adherence to ART and HBV‐active medications. The counseling will emphasize how consistent medication use contributes to improved virological outcomes, reduced risk of disease progression, prevention of drug resistance, and better overall health outcomes.

### Outcome Measures

2.10

#### Primary Outcome

2.10.1

HIV viral load will be measured at baseline and at the end of the 6‐month follow‐up period in both the intervention and comparison groups. The primary outcome will be assessed as the change in log‐transformed HIV viral load (log_10_ copies/mL) from baseline to endline, enabling quantification of the magnitude of virological response over time. The intervention effect will be evaluated by comparing the mean change in log‐transformed viral load between the intervention and comparison groups using a pre–post analytical framework.

In addition, virological suppression (VS) will be evaluated as an important clinical outcome and will be defined as an HIV viral load of < 1000 copies/mL, based on the most recent viral load measurement obtained within 30 days before or after the scheduled 6‐month follow‐up assessment. Assessments will be conducted at equivalent time points in both groups to ensure a comparable observation window. Data on viral load will be obtained from patient medical records and laboratory viral load testing reports.

#### Secondary Outcomes

2.10.2

##### Medication Adherence

2.10.2.1

Medication adherence will be assessed at baseline and at the scheduled 6‐month follow‐up visit in both the intervention and comparison groups using a context‐adapted version of the Hill‐Bone Medication Adherence Scale (HBMAS) [23]. Medication adherence will be evaluated over the same 6‐month post‐enrollment follow‐up period used for assessment of the primary outcome, ensuring a comparable observation window across study arms.

The HBMAS is a validated self‐report instrument designed to assess adherence behaviors among individuals receiving long‐term therapy and has been adapted to capture adherence to ART and HBV‐active medications among adults living with HIV or HIV–HBV co‐infection [23, 24]. The adapted HBMAS assesses three domains of adherence: medication‐taking behavior, appointment keeping, and prescription refilling. Responses are recorded using a Likert‐type scale, and item scores are summed to generate a total adherence score, with higher scores indicating poorer adherence.

##### Knowledge Change

2.10.2.2

Knowledge regarding HIV–HBV co‐infection will be assessed using a structured questionnaire administered at baseline and at the end of the 6‐month follow‐up period in both the intervention and comparison groups. Knowledge scores will be calculated by summing correct responses to generate a composite score, with higher scores indicating better disease‐related knowledge.

